#### **7.8.4 Cellular Immunology Assays**

Lymphocyte proliferation assays will be performed using blood collected at various time points in the study, by separating peripheral blood mononuclear cells (PBMCs) from whole blood and culturing cells with media only, the mitogen phytohemagglutinin, or the antigen *Na*-GST-1. At the end of the culture period, the cells will be pulsed with [H]-thymidine, harvested, and the incorporated thymidine level detected using a beta-counter. Stimulation indices will be calculated and compared to a control consisting only of media.

Cytokines (e.g., IL-2, IL-4, IL-5, IL-10, TNF $\alpha$ , and IFN $\gamma$ ) will be quantified using Cytometric Bead Analysis kits of supernatants collected from PBMCs stimulated with *Na*-GST-1 antigen for 48 and 72 hours *in vitro*. Chemokines (e.g., RANTES, MIP1a, MCP-1, and IP-10) will be quantified in supernatants using commercially available ELISA kits. Flow cytometric analysis of cell surface markers (phenotyping) of whole blood will also be performed to evaluate the frequency and distribution of different cell types.

#### **7.8.5 Storage of Participant Specimens**

Extra samples of serum, plasma, and feces will be stored for at least five years, in case future questions arise regarding the safety or immune response to the vaccine. Extra lymphocytes will be cryopreserved for future development of human monoclonal antibodies to be used for future immunoassays. Prior to conducting any future tests on stored samples that are not described in this protocol, permission will first be obtained from the IRBs.

### **7.9 Stool Examination**

Fecal exams will begin with an ether sedimentation assay to determine infection status (positive or negative). In Part II of the study, positive samples will undergo Kato Katz fecal thick smear exams to determine infection intensity (eggs per gram of feces).

## 8 ADVERSE EVENTS MONITORING AND REPORTING

### 8.1 Definitions

#### 8.1.1 Adverse Event

An adverse event (AE) includes any noxious, pathological or unintended change in anatomical, physiological or metabolic functions as indicated by physical signs, symptoms and/or laboratory-detected changes occurring in any phase of the clinical study, whether associated with the study vaccine or active comparator, and whether or not considered vaccination related. This includes an exacerbation of pre-existing conditions and intercurrent illnesses. All AEs must be graded for severity and relationship to the study vaccine as described in **Section 8.2.2** and **Section 8.2.3** in this protocol.

#### 8.1.2 Serious Adverse Event (SAE)

An SAE is an AE, whether considered related to the study vaccine or not, meeting one of the following conditions:

1. Death during the period of protocol-defined surveillance
2. Life threatening: defined as an event that places a subject at immediate risk of death at the time of the event and does not refer to an event that hypothetically might have caused death were it more severe
3. Hospitalization during the period of protocol-defined surveillance: defined as at least an overnight stay in the hospital or emergency ward for treatment that would have been inappropriate if administered in the outpatient setting
4. Results in a congenital anomaly or birth defect
5. Results in a persistent or significant disability or incapacity: defined as a substantial disruption of the study participant's ability to carry out normal life functions
6. Any other important medical event that may not result in death, be life threatening, or require hospitalization, may be considered a serious AE when, based upon appropriate medical judgment, the event may jeopardize the subject and may require medical or surgical intervention to prevent one of the outcomes listed above.

#### 8.1.3 Adverse Events of Special Interest (AESIs)

Special attention will be paid to monitoring for the occurrence of certain adverse events termed, "Adverse Events of Special Interest" or AESIs. These include inflammatory and autoimmune disorders that may potentially be related to the use of an immunostimulatory adjuvant (although none have been associated with the use of GLA-AF). The occurrence of the following AESI's will be closely monitored:

- Neuroinflammatory disorders (optic neuritis, multiple sclerosis, demyelinating disease, transverse myelitis, Guillain-Barre syndrome, myasthenia gravis, encephalitis, neuritis, Bell's palsy)
- Musculoskeletal disorders (systemic lupus erythematosus, cutaneous lupus, Sjogren's syndrome, scleroderma, dermatomyositis, polymyositis, rheumatoid arthritis, juvenile

rheumatoid arthritis, polymyalgia, rheumatica, reactive arthritis, psoriatic arthropathy, ankylosing spondylitis, spondylarthropathy)

- Gastrointestinal disorders (Crohn's disease, ulcerative colitis, celiac disease)
- Metabolic diseases (autoimmune thyroiditis, Grave's or Basedow's disease, Hashimoto thyroiditis, insulin-dependent diabetes mellitus, Addison's disease)
- Skin disorders (psoriasis, vitiligo, Raynaud's phenomenon, erythema nodosum, autoimmune bullous skin diseases)
- Others (autoimmune hemolytic anemia, idiopathic thrombocytopenic purpura, antiphospholipid syndrome, temporal arteritis, Behcet's syndrome, pernicious anemia, autoimmune hepatitis, primary biliary cirrhosis, primary sclerosing cholangitis, autoimmune glomerulonephritis, autoimmune uveitis, autoimmune cardiomyopathy, sarcoidosis, Stevens-Johnson syndrome).
- Vasculitides

## **8.2 Assessment of Adverse Events**

### **8.2.1 Identification of AEs**

Assessment of safety will include clinical observation and monitoring of hematological, blood chemistry, and immunologic parameters. Safety will be evaluated by monitoring of participants for local and systemic adverse reactions during the course of the trial. Participants will be closely monitored for at least 2 hours following each immunization. Additionally, participants will be evaluated on Days 1, 3, 7, 14 and 28 following each vaccination for clinical assessments.

All AEs will be graded for severity and relationship to study vaccine. Reactions will be graded as described in **Section 8.2.2** in this protocol. During Part II of the study, a study clinician will stay in or near Americaninhas for the duration of the trial and will be available to the study participants at all times. Should a participant call on a study clinician to report an AE, it will be fully documented in their study chart, and discussed with the Principal Investigator.

### **8.2.2 Determination of Severity**

All AEs will be assessed by the investigator using the following protocol-defined grading system:

|          |                                                                                                                                                         |
|----------|---------------------------------------------------------------------------------------------------------------------------------------------------------|
| Grade 0: | None                                                                                                                                                    |
| Grade 1: | Mild - No effect on activities of daily living; no medical intervention/therapy required                                                                |
| Grade 2: | Moderate - Partial limitation in activities of daily living (can complete $\geq 50\%$ of baseline); no or minimal medical intervention/therapy required |
| Grade 3: | Severe - Activities of daily living limited to $< 50\%$ of baseline; medical evaluation/therapy required                                                |
| Grade 4: | Potentially life threatening                                                                                                                            |

Intensity of the following AEs will be assessed by the investigator as described in **Table 4**. All laboratory AEs will be graded in severity following the toxicity table in **Appendix C**. Unsolicited adverse events and clinically significant laboratory abnormalities not described in **Table 4** or **Appendix C** will be graded according to **Appendix D**.

**Table 4: Assessment of Adverse Event Severity**

| Adverse Event                         | Grade                 | Severity                                                                                                                                                                                                                                                                  |
|---------------------------------------|-----------------------|---------------------------------------------------------------------------------------------------------------------------------------------------------------------------------------------------------------------------------------------------------------------------|
| Pain at injection site                | 0
1
2
3
4 | None
Easily tolerated, does not interfere with activity
Repeated use of non-narcotic pain reliever for > 24 hours or interferes with daily activity
Any use of narcotic pain reliever or prevents daily activity
Emergency room (ER) visit or hospitalization |
| Tenderness at injection site          | 0
1
2
3
4 | None
Mild discomfort to touch
Discomfort with movement
Significant discomfort at rest
ER visit or hospitalization                                                                                                                                             |
| Erythema at injection site            | 0
1
2
3
4 | < 25 mm
25 mm - 50 mm
51 mm - 100 mm
> 100 mm
Necrosis or exfoliative dermatitis                                                                                                                                                                              |
| Induration/swelling at injection site | 0
1
2
3
4 | <25 mm
25 mm - 50 mm and does not interfere with daily activity
51 mm - 100 mm or interferes with daily activity
>100 mm or prevents daily activity
Necrosis                                                                                                  |
| Fever (oral)                          | 0
1
2
3
4 | <38.0°C
38.0°C - 38.4°C
38.5°C - 38.9°C
39.0°C – 40.0°C
>40.0°C                                                                                                                                                                                               |
| Headache                              | 0
1
2
3
4 | None
Easily tolerated, does not interfere with daily activity
Repeated use of non-narcotic pain reliever for >24 hours or interferes with daily activity
Any use of narcotic pain reliever or prevents daily activity
ER visit or hospitalization             |
| Nausea                                | 0
1
2
3
4 | None
Easily tolerated, does not interfere with daily activity
Interferes with daily activity
Prevents daily activity
ER visit or hospitalization                                                                                                              |
| Vomiting                              | 0
1
2
3
4 | None
1-2 episodes in 24 hours and does not interfere with activity
> 2 episodes in 24 hours or interferes with daily activity
Prevents daily activity or requires outpatient IV hydration
ER visit or hospitalization for hypotensive shock                   |
| Myalgia                               | 0
1
2
3
4 | None
Easily tolerated, does not interfere with daily activity
Interferes with daily activity
Prevents daily activity
ER visit or hospitalization                                                                                                              |
| Arthralgia                            | 0
1
2
3
4 | None
Easily tolerated, does not interfere with activity
Interferes with daily activity
Prevents daily activity
ER visit or hospitalization                                                                                                                    |

|                             |   |                                                                               |
|-----------------------------|---|-------------------------------------------------------------------------------|
| Urticaria                   | 0 | None                                                                          |
|                             | 1 | Requiring no medications                                                      |
|                             | 2 | Requiring PO or topical treatment, or IV medication or steroids for <24 hours |
|                             | 3 | Requiring IV medication or steroids for >24 hours                             |
|                             | 4 | ER visit or hospitalization                                                   |
| Mucocutaneous Reaction/Rash | 0 | None                                                                          |
|                             | 1 | Erythema; pruritus or localized macular rash                                  |
|                             | 2 | Diffuse, maculo-papular rash, dry desquamation                                |
|                             | 3 | Vesiculation or moist desquamation or ulceration                              |
|                             | 4 | Necrosis                                                                      |

### 8.2.3 Association with Receipt of the Study Vaccine

All AEs will have their possible relationship to study vaccine assessed using the following terms:

- Definite: Clear-cut temporal association, and no other possible cause.
- Probable: Clear-cut temporal association and a potential alternative etiology is not apparent.
- Possible: Less clear temporal association; other etiologies also possible.
- Unlikely: Temporal association between the AE and the vaccine or the nature of the event is such that the vaccine is not likely to have had any reasonable association with the observed illness/event (cause and effect relationship improbable but not impossible).
- Not Related: The AE is completely independent of vaccine administration; and/or evidence exists that the event is definitely related to another etiology.

The degree of certainty with which an AE can be attributed to administration of the study vaccine will be determined by how well the event can be understood in terms of one or more of the following:

1. The event being temporally related with vaccination or reproduced on re-vaccination.
2. A reaction of similar nature having previously been observed with this type of vaccine and/or formulation.
3. The event having often been reported in the literature for similar types of vaccines.

All local (injection-site) reactions will be considered definitely related to vaccination.

## 8.3 Adverse Event Reporting

All SAEs will be reviewed by a study physician, recorded on the appropriate SAE form, and followed through to resolution or stabilization by a study physician. All SAEs will be reported by email, telephone or fax within 1 working day of notification of the SAE occurrence to the Principal Investigator, to all of the following:

- Sponsor (Office of Vaccine Operations, Sabin Vaccine Institute): [contact], [contact]
- Centro de Pesquisa René Rachou Ethics Committee: [contact], [contact]
- GWUMC Institutional Review Board (IRB): [contact], [contact]

Following notification from the investigator, SVI as the sponsor of the investigational product, will report events that are both serious and unexpected that are possibly, probably, or definitely related to the vaccine, to the FDA and ANVISA within the required timelines: fatal and life-threatening events within 7 calendar days (by phone, fax, or internet) and all other SAEs in writing within 15 calendar days. All SAEs not listed as possibly, probably, or definitely related will be reported to the FDA and ANVISA at least annually in a summary format.

All AESIs will be reported to Sponsor and to the FDA and ANVISA according to the same procedure as for reporting SAEs, and according to the same timelines as described above.

All local and systemic reactions not meeting the criteria for “serious adverse events” will be captured on the appropriate case report form (CRF). These events will be followed to resolution. Grade 3 adverse events deemed definitely or probably related to vaccination will be reported by email or fax within 15 working days of the Principal Investigator becoming aware of the event, to the Sponsor and the Safety Monitoring Committee.

## **8.4 Adverse Event Monitoring**

### ***8.4.1 Medical Monitor***

An independent medical monitor will be appointed for oversight of participant safety in this trial. The Monitor for Part I of the study may be different than the one for Part II, due to the distance between the sites. The Medical Monitor(s) will be available to advise the investigators on trial-related medical questions or problems. Should the Monitor(s) not be available, they will recommend an alternative to serve as a substitute independent Medical Monitor.

The Medical Monitor’s primary responsibility will be to monitor participant safety. The Principal Investigator is responsible for ensuring that the Medical Monitor is aware of any new safety information that becomes available during the course of the trial.

### ***8.4.2 Safety Monitoring Committee (SMC)***

SVI will select at least three individuals (one of whom will be the independent Medical Monitor) to advise SVI and the study investigators on the trial. These individuals will be independent from SVI and the Human Hookworm Vaccine Initiative (HHVI). Individuals may be affiliated with GWU or FIOCRUZ if their affiliation is unrelated to the SVI Product Development Partnership and HHVI. The SMC’s primary responsibility will be to monitor participant safety. The Principal Investigator is responsible for ensuring that the SMC is aware of all new safety information. The SMC will periodically review data on safety and enrollment, and will review cumulative safety data for evidence of study related AEs, adherence to the protocol, and factors that may affect outcome or study data such as protocol violations and losses to follow up.

All cumulative safety data reports from the trial will be submitted to the SMC before beginning vaccinations in Part II of the study as well as before each dose escalation in Part II (i.e., between the first dose in Cohort 7 and Cohort 9 and the first dose in Cohort 9 and Cohort 11, and so on). Safety data reports will include data from at least the first 7 days after vaccination. After the third and final vaccination has been administered to all dose cohorts, additional safety and immunology results and reports will be submitted to the SMC as they become available. A final report will be submitted to the SMC following completion of the study.

Conference calls between the investigators and the SMC will be scheduled at least one week prior to beginning Part II of the study and prior to each dose escalation in Part II (i.e., after the first dose is administered to Cohort 7 but before the first dose is administered to Cohort 9, etc.). If no criteria for suspending the study are met (see **Section 8.5**), vaccinations will proceed with approval from the SMC. During Part II of the study, should the SMC not be able to meet in a timely fashion, the SMC may reserve the right to defer to the independent Medical Monitor to decide whether or not dose escalation may proceed.

Written approval (via fax or email) to proceed to Part II of the study or to the next dose concentration of vaccine must be obtained from the SMC (or Medical Monitor during Part II in the event that the SMC cannot review the safety data in a timely manner, as described above) prior to administration. Both the SMC and Medical Monitor will have access to the randomization code for Part II of the study, as they may wish to review the data in an unblinded fashion should significant safety questions arise prior to the final unblinding.

It is the Principal Investigator's (or designated agent) responsibility to ensure that the SMC reviews the current safety data (grouped by dose cohort), study protocol, and any other requested documents at its meetings. Occurrence of an SAE will be reported to the SMC at the same time that it is reported to the IRBs/IECs. Additionally, any new information that may adversely affect the safety of the subjects or the conduct of the study will be submitted to the SMC as it becomes available.

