Prior to enrolling and vaccinating volunteers in Part II of the study, safety data up to and including Day 70 post-vaccination from the sixth cohort (i.e., the cohort administered 100 µg *Na*-GST-1/Alhydrogel®/GLA-AF) will be reviewed by the Safety Monitoring Committee (SMC). The trial will not proceed to Part II of the study if any of the stopping criteria listed in **Section 8.5** are met, or if in the clinical judgment of the SMC, continued enrollment and vaccinations would pose an unacceptable safety risk to the participants.

In Part II of the study, prior to dose escalation (e.g., after enrolling Cohort 7 but before enrolling Cohort 9), safety data up to and including Day 7 post-vaccination will be compiled from the lower dose cohort for review by the Medical Monitor and/or SMC. The trial will not proceed to the next dose cohort if any of the stopping criteria listed in **Section 8.5** are met or, in the clinical judgment of the SMC and/or Medical Monitor, the next higher dose would pose an unacceptable safety risk to the participants.

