| 20                                         |                                                                                                                                               |                                                                                                                                                                                                          |                                                                                                                                                | Vaccination 3
(Day 112)                                                                                                                                                                                  | Vaccination 3
(Day 112)                                                                                                                       |                                                                                                                                                                                                               |
| 21                                         |                                                                                                                                               |                                                                                                                                                                                                          |                                                                                                                                                |                                                                                                                                                                                                             |                                                                                                                                                  | Vaccination 3
(Day 112)                                                                                                                                                                                    |

Approximate (see **Section 7.6** for more detail). Weeks between enrollment of successive cohorts are the minimum required.

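### Table 3's minimum of about 7 days between Cohorts 10 and 12 is too short for the Day 7 safety review that Sections 4.1 and 8.4.2 require before a dose escalation

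*Protocol*

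**What the plan says.** Section 4.1 sets the Part II review, done by the Medical Monitor and/or the SMC before the dose is raised: "safety data up to and including Day 7 post-vaccination will be compiled from the lower dose cohort for review". It gives one pair as an example ("e.g., after enrolling Cohort 7 but before enrolling Cohort 9"). It then states a general bar, with the criteria taken from Section 8.5: "The trial will not proceed to the next dose cohort if any of the stopping criteria listed in".

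Section 8.4.2 says that cumulative safety reports go to the SMC before Part II "as well as before each dose escalation in Part II". It then specifies the points, after i.e., as "between the first dose in Cohort 7 and Cohort 9 and the first dose in Cohort 9 and Cohort 11, and so on". Each report must cover at least the first 7 days after vaccination. SMC conference calls "will be scheduled at least one week prior to beginning Part II of the study and prior to each dose escalation in Part II". Written approval from the SMC, or from the Medical Monitor if the SMC cannot review in time, is needed before the next concentration of vaccine is given.

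Table 3 places first doses at week 0 (Cohort 7), week 2 (Cohorts 8 and 9), week 4 (Cohorts 10 and 11) and week 5 (Cohort 12). Its footnote calls the times approximate and adds: "Weeks between enrollment of successive cohorts are the minimum required". Section 7.6 gives the Day 7 visit a window of plus or minus 1 day.

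**The concern.** The review must use Day 7 data, but the schedule allows the next dose about 7 days after the lower one. This occurs at only one Part II dose step: from 30 to 100 µg with GLA-AF in hookworm-exposed adults. Section 1.12 says the safety profile may differ in this population. Sections 1.11 and 11.3.3 anticipate somewhat more local reactions with this class of adjuvant.

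The review text does not clearly settle the conflict. The cohorts named in Section 8.4.2 (7, 9 and 11) are those given Alhydrogel alone or the comparator. Approval attaches to an antigen concentration, and 100 µg is opened by Cohort 11, which starts in the same week as Cohort 10. A site that works from the named pairs and the approval sentence could treat Cohort 12 as already cleared and follow the one-week minimum. A site that works from Section 4.1 could not. A safety review before escalation should not depend on which paragraph a site follows.

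**Working it through.** **Inputs.** First-dose weeks are from Table 3. The data cut (through Day 7) is from Section 4.1 and the visit window (Day 6 to Day 8) from Section 7.6. Cohort sizes are from Table 1. A calendar week is taken as 7 days, and each cohort as injected on one day, as Section 4.3 implies.

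**Is week 5 for Cohort 12 a misprint?** Its second and third doses are at weeks 13 and 21. 13 − 5 = 8 weeks (56 days) and 21 − 5 = 16 weeks (112 days), matching the Day 56 and Day 112 schedule. The entry is internally consistent.

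**Minimum gap** = (week of higher-dose cohort − week of lower-dose cohort) × 7 days. **Time left after the Day 7 visit** = gap − day of visit.

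| Dose step | Formulation | Gap (days) | Left if visit on Day 6 / 7 / 8 |
|---|---|---|---|
| 7 to 9 | Alhydrogel | (2 − 0) × 7 = 14 | 8 / 7 / 6 |
| 8 to 10 | with GLA-AF | (4 − 2) × 7 = 14 | 8 / 7 / 6 |
| 9 to 11 | Alhydrogel | (4 − 2) × 7 = 14 | 8 / 7 / 6 |
| 10 to 12 | with GLA-AF | (5 − 4) × 7 = 7 | 1 / 0 / −1 |

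Compilation, review and written approval must all fit into the last column. Three steps leave about a week. The step from Cohort 10 to Cohort 12 leaves one day at best, and with a Day 8 visit the data do not yet exist.

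**Could the review before Cohort 11 serve for Cohort 12?** Cohorts 10 and 11 both start in week 4, a gap of (4 − 4) × 7 = 0 days. That review therefore contains no Cohort 10 data.

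**Does the same problem affect the step from Cohort 8 to Cohort 10?** Cohort 8 starts in week 2 with Cohort 9. The named review before Cohort 11 uses cumulative data, so Cohort 8's first week should be available to it, and Cohort 10 starts in the same week as Cohort 11. In practice that step is covered, although it is not named.

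**Participants affected.** Section 4.1 asks for the lower dose cohort. For Cohort 12 with GLA-AF that is Cohort 10: 12 people, 10 of them given 30 µg plus GLA-AF. Cohort 12 has 12 people, 10 of them given 100 µg plus GLA-AF.

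**One-week lead for the call.** If the lead stated for Part II also governed each escalation, the time remaining would be gap − 7 − 7: 0 days for the 14-day steps and −7 days for Cohort 10 to Cohort 12. The sentence can be read either way, so this result is conditional.

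**The case against.** The strongest reply is that a minimum interval does not waive a review. Both sections state the requirement generally, Section 4.1 gives its pair only as an example, and the list in Section 8.4.2 is left open at the end. After Cohort 11 no odd-numbered cohort remains, so the open ending most naturally points to the GLA-AF steps. Table 3's times are approximate, and if the review is not complete Cohort 12 waits. This stands. A reader might infer that the protocol authorises Cohort 12 before review, or that the safeguard is absent; the text supports neither.

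The stakes also have limits. Part I gives GLA-AF to 18 people, six of them at 100 µg, and the SMC reviews Cohort 6 through Day 70 before Part II. Section 4.1 expects hypersensitivity within 24 hours and other severe reactions within 72 hours, so the Day 1 and Day 3 visits precede Cohort 12 even at the 7-day gap. The suspension criteria in Section 8.5 do not depend on scheduled reviews. All of this stands, but the protocol chose Day 7 as its data cut, and a Medical Monitor acting for the SMC needs the same data.

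Three larger claims are tempting but not supported. Adding Cohort 11 to make 22 affected people goes beyond Section 4.1, because Cohort 11 has the same antigen dose as Cohort 12. A required interval of 14 to 15 days depends on the doubtful reading of the call sentence, which would also leave the other steps with no time to spare. Requiring both Cohort 10 and Cohort 11 data before Cohort 12 would be a new rule, not one found in the protocol.

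**Conclusion.** The point holds as a conflict between the schedule and the review. Table 3's minimum for Cohort 12 is half that of every other Part II dose step and leaves between +1 and −1 day after the Day 7 visit for compilation, review and approval. At that minimum, up to 12 Cohort 10 participants could have incomplete or unreviewed Day 7 data when Cohort 12 is injected. The general text supports reviewing before Cohort 12, but the named pairs and the link between approval and concentration leave room to read it as already cleared.

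The 12 is an upper bound: it assumes that the site uses the stated minimum and reads a calendar week as 7 days. A site that waits for the review would have no such gap, but would start later than the minimum printed in Table 3.

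**What to change.** Reconcile Table 3 with Sections 4.1 and 8.4.2. The text should state:

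- whether the steps from Cohort 8 to Cohort 10 and from Cohort 10 to Cohort 12 are review points;
- which cohorts' data each review uses;
- whether written approval is given by antigen concentration or by cohort and formulation;
- whether the one-week lead for the SMC call applies to each escalation or only to the start of Part II.

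Table 3's minimum for Cohort 12 should then agree with the result. The sponsor and the SMC set the interval; this review proposes none.

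The cost is amendment wording and one table row, with its later doses if the start moves. The downside is a possible short delay to one cohort in a trial planned for 24 months.
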